**Fig. 1 Fig1:**
[figure not shown]
Schedule of enrolment, intervention and assessments

### Treatment of participants

#### Group A: Standard of care

NIV should be applied after a maximum of 2 hours from ICU admission using ICU ventilators with NIV-dedicated software. Use of full-face mask is recommended. Initial inspiratory positive airway pressure (IPAP) of 10 cmH_2_O and positive end-expiratory pressure (PEEP) of 5 cmH_2_O is recommended. IPAP may be then gradually increased by 2-5 cmH_2_O increments at a rate of approximately 5 cmH_2_O each 10 minutes until arterial pH>7.30 and patient tolerability has been reached. Inspiratory O_2_ fraction should be adjusted to maintain an O_2_ saturation of 88-92%.

Escalation to invasive mechanical ventilation should be considered by the attending physician (not involved in the study) when two of the following occur for at least 2 hours (‘urgency criteria’):
respiratory rate >35 breaths/ min; arterial pH<7.25;PaCO_2_ greater than 60 mmHg;PaO_2_ less than 60 mm Hg with an FiO_2_ greater than 60%;respiratory arrest or signs of patient distress with accessory muscle recruitment and paradoxical abdominal or thoracic motion.

In addition, intubation will be immediately performed when any of the following is observed (‘emergency criteria’):
hemodynamic instability (defined as 80-90 mmHg increase or a 30-40 mmHg decrease in systolic blood pressure relative to the baseline value or need for vasopressors to maintain systolic blood pressure > 85 mmHg or electrocardiographic evidence of ischemia or significant ventricular arrhythmias);need for sedation for major agitation (Richmond Agitation Sedation Scale ≥ 3) [40];acute neurological dysfunction (Kelly-Matthay score > 3) [41];cardiac arrest.

Patients should undergo a formal assessment of discontinuation from mechanical ventilation (invasive or non-invasive) and daily spontaneous breathing trials (SBT) will be performed to identify patients able to wean from mechanical ventilation once the cause of the exacerbation is adequately treated, the patient is hemodynamically stable (see above criteria for hemodynamic instability) and there are no signs of change in mental status (e.g., somnolence, coma, agitation, anxiety), onset or worsening of discomfort, diaphoresis, signs of increased work of breathing (use of accessory respiratory muscles, and thoracoabdominal paradox) *and* at least two of the following parameters are met:
minute ventilation <15 l/min;PaO_2_/FiO_2_ ratio > 150 to 200; with PEEP ≤ 5 cmH_2_OFiO_2_ ≤ 0.4;pH > 7.30rapid shallow breathing index < 105 [42]

Pressure support ventilation (PSV) will be used to gradually decrease mechanical ventilatory support. Patient will be defined as “weaned from mechanical ventilation” (invasive or non-invasive) if the following 4 criteria are met for the last 30 minutes during a spontaneous breathing trial (SBT):
SpO_2_≥90% and/or PaO_2_≥60 mmHg (PaO_2_ to take precedence if both available)Respiratory rate ≤30 bpmpH ≥ 7.35No respiratory distress (defined as 2 or more of the following):
Heart rate ≥ 120% of the 6:00 a.m. rate for ≥5 minutesSignificant use of accessory musclesAbdominal paradoxDiaphoresisMarked dyspnea as subjectively assessed by the investigator

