### Inclusion criteria

Patients older than 18 and younger than 90 yearsDocumented clinical history of COPDICU admission for exacerbation of COPD requiring NIV support

After two hours of NIV at least two of the following criteria for high risk of NIV-failure [14, 22] must be fulfilled:
arterial pH ≤ 7.25respiratory rate ≥30 breaths/minuse of accessory muscles or paradoxical abdominal movements

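### Respiratory arrest is listed among the slower, discretionary intubation triggers and is missing from the list for immediate intubation

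*Protocol article*

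**What the plan says.** The intubation criteria are in the protocol article under Group A: Standard of care, in two tiers.

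- **Urgency.** The trigger is met "when two of the following occur for at least 2 hours", and its consequence is discretionary: "Escalation to invasive mechanical ventilation should be considered by the attending physician (not involved in the study"). The list has five items: respiratory rate, arterial pH, PaCO2, oxygenation, and a fifth that reads "respiratory arrest or signs of patient distress with accessory muscle recruitment and paradoxical abdominal or thoracic motion".
- **Emergency.** "intubation will be immediately performed when any of the following is observed". Four items follow: hemodynamic instability, "need for sedation for major agitation", "acute neurological dysfunction (Kelly-Matthay score > 3"), and cardiac arrest.

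The section on Group B adopts the Group A intubation criteria without change, so one rule governs both arms.

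**The concern.** The fifth urgency item joins two very different states with an 'or'. Signs of distress develop and persist, so a 2-hour observation rule can be applied to them. Respiratory arrest is immediately life-threatening. Read as written, it counts as one of the two items needed, must last at least 2 hours, and then leads only to escalation being considered. Agitation that needs sedation, by contrast, leads to immediate intubation on its own.

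What is at stake is a written safety rule in a trial of ventilatory failure. The respiratory event that most needs an immediate instruction is the one without it. No effect on outcomes, power or analysis is claimed.

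**Working it through.** No arithmetic is involved and the plan states no figure to reproduce. The check sets the two tiers side by side and follows a respiratory arrest through each.

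| | Urgency tier | Emergency tier |
|---|---|---|
| Number of items listed | 5 | 4 |
| Items needed | 2 | 1 |
| Duration needed | at least 2 hours | none |
| Resulting action | escalation considered | immediate intubation |
| Respiratory arrest listed | yes, in item 5 | no |
| Cardiac arrest listed | no | yes |

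1. **Is the placement an effect of text extraction?** No. The bullets are run together, but each tier has its own lead-in sentence and label, and the item comes before the emergency lead-in.

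2. **Does another section correct it?** No. The term respiratory arrest occurs once in the article, in this item. Group B refers back to Group A. The Safety section reuses only the definition of hemodynamic instability.

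3. **Does the urgency rule work for an arrest?** No. An arrest alone is one item where two are needed. Adding a second item does not help, because the 2-hour condition still applies and an arrest cannot be observed for 2 hours.

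4. **Does the urgency rule work for distress?** Yes. Distress can persist for hours. A closely related sign, "accessory muscles or paradoxical abdominal movements", is itself one of three entry criteria assessed on a similar time scale: "After two hours of NIV at least two of the following criteria for high risk of NIV-failure". The two items are not identical. The entry item accepts either sign, while the urgency item asks for accessory muscle recruitment together with paradoxical motion.

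5. **Which patients fall in the gap?** A patient who arrests after 2 hours of qualifying distress plus a second urgency item has already met the urgency rule. The gap is therefore an arrest without that lead-in, and it lasts until an emergency item such as neurological dysfunction or cardiac arrest appears. Enrolled patients may already show distress, but enrolment does not by itself meet the urgency rule. The entry thresholds are looser: pH ≤ 7.25 against < 7.25, respiratory rate ≥ 30 against > 35, and either sign against both.

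6. **Does any trial figure depend on it?** No. The sample size inputs (284 patients, 90% power, hazard ratio 0.67, significance level 0.05) do not involve the intubation criteria. In the primary outcome, prolonged ventilation counts invasive and non-invasive support alike. Intubation is a secondary outcome, under the same criteria in both arms.

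**The case against.** The strongest reply is that no clinician would apply the literal reading. The urgency sentence says when escalation should be considered; it imposes no minimum wait and forbids nothing earlier. The decision belongs to an attending physician outside the study, so ordinary judgement remains in force. The emergency list is introduced as an addition and is not said to be exhaustive, and a patient who stops breathing would probably soon meet one of its items. All of this stands, and it is why the point is minor. It does not make the wording right. The emergency tier exists to remove discretion for immediately life-threatening events, and waiting for coma or cardiac arrest is the deterioration that an immediate rule is meant to prevent.

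A second reply is that 'arrest' may be a slip for 'distress', which would fit the rest of the item. The article does not settle this. The remedy does not depend on it: with distress in the urgency list and arrest in the emergency list, the rule is sound whichever word was meant.

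**Conclusion.** The concern holds as a minor patient-safety correction. Respiratory arrest sits in the tier that needs two items and at least 2 hours before escalation is considered, and it is absent from the tier where one item suffices with no waiting time. That this is the wrong tier rests on a clinical judgement, that an arrest needs an immediate response, and on the plain fact that it cannot be observed for 2 hours.

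In practice the gap is narrow, as described in step 5 of the working. How soon another emergency item would appear is clinical inference, not something the article states. The article gives no frequency of respiratory arrest, so the number of patients affected is unknown. The rule is the same in both arms, so the wording does not by itself favour either one.

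**What to change.** Under Group A: Standard of care, make one edit in two places:

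- In the emergency list, change the fourth item from 'cardiac arrest' to 'cardiac or respiratory arrest'.
- In the urgency list, delete the mention of respiratory arrest from the fifth item and leave the signs of distress as they stand.

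Respiratory arrest then needs one item and no waiting time. The lists stay at 5 and 4 items, and the two-of-five rule for distress is unchanged. The Group B section needs no edit because it refers back to Group A. The Safety section needs none because the hemodynamic instability definition is untouched.

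The cost is one wording change, with no effect on sample size, outcomes or analysis. According to Trial status, recruitment had not begun when the article was written, so the change could have been made before any patient was enrolled.

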#### Group B: Standard of care plus ECCO_2_R

NIV is applied and managed with the same modalities and at the same conditions as in Group A (standard of care).

After setting NIV, percutaneous vascular access is provided using a double lumen catheter inserted in the internal jugular vein or in the femoral vein (14F, Joline GmbH & Co. KG, Germany). An ECCO_2_R device will be used (DECAPsmart, Medica S.p.A.- Intensivecare s.r.l., Salerno, Italy). Blood flow is driven by a roller nonocclusive pump (0–450 mL/min) through a polymethylpentene artificial lung (priming volume, 200 mL; contact surface area, 0.8 m^2^; maximum blood flow rate, 450 mL/min) that is connected to a fresh gas flow source delivering 100% oxygen at a constant rate of 8 L/min. A starting dose of heparin (80 IU/kg bolus followed by ∼18 IU/kg/ hour infusion) will be delivered by using a syringe pump included in the system. Continuous infusion of heparin is hence titrated to maintain values of activated partial thromboplastin time (aPTT) in the range 35-80 sec or aPTT ratio of 1.5-2.0; aPTT is checked approximately every 2-3 hours during the first 6 hours from therapy initiation; afterwards, aPTT is checked every 6 hours. ECCO_2_R will be continued for at least 24 hours.

Intubation criteria are the same as in Group A (standard of care).

Weaning from ECCO_2_R must always precede weaning from mechanical ventilation. ECCO_2_R will be interrupted while keeping mechanical ventilation (invasive or non-invasive) when all of the following are achieved for at least 12 hours:
respiratory rate<25 breaths/min;pH>7.35;arterial PCO_2_<20% of the baseline value;absence of use of the accessory muscles or paradoxical abdominal movements.

Criteria to (a) *run formal assessment of discontinuation* from mechanical ventilation (invasive or non-invasive) through a daily spontaneous breathing trial (SBT); (b) to be defined as “weaned from mechanical ventilation” (invasive or non-invasive) are the same as in Group A (standard of care).

Use of ECCO_2_R is stopped and device (and catheter) removed in the following situations:
Air embolus in the extracorporeal circuitCircuit clotting leading to an abrupt stop of extracorporeal blood flowDevice malfunction leading to abrupt stop of extracorporeal blood flowSevere thrombocytopenia (< 29,000/mm^3^)Fibrinogen < 1g/L or fibrinogen < 1.5 g/L with diffuse bleedingAnytime the physician in charge believes that the protocol may be compromising patient’s outcome

Interruptions of ECCO_2_R (for any cause) lasting longer than 6 hours are to be considered ‘treatment failure’ and lead to termination of the experimental protocol.

All concomitant therapies foreseen by the standard of care of enrolled patients are allowed.

Post-trial care will be delivered according to the standard of care for AECOPD patients.

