Extracorporeal circuits designed to remove CO_2_ (ECCO_2_R) may add to improved efficacy of NIV by removing CO_2_ [12–15] and avoid worsening of respiratory acidosis [16–18]. Although available studies are limited to case series [12], several ECCO_2_R devices have been developed and proposed for the clinical use in patients with COPD [19]. These systems often represent modifications of renal replacement therapy circuits and are characterized by: (a) veno-venous by-pass systems; (b) extracorporeal blood flow of 0.3-0.5 liters/min; (c) 13 Fr bore catheters or a single co-axial catheter; (d) very low heparin doses or no heparin; (e) minimal volumes for circuit priming; (f) artificial membrane lung connected to a source of 100% O_2_ (usual flow 6-8 liters/min). These systems are able to reduce PaCO_2_ by 20-25% [20, 21]. These circuits have evolved in time and may be efficient even when using relatively small-bore catheters and low blood flows [19]. These modifications may reduce the side effects that have complicated earlier studies and underscore the rationale to perform this study.

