### Primary outcome

The primary outcome is event free survival, defined as survival at day 28 free of any of the following: (a) prolonged mechanical ventilation; (b) development of septic shock; (c) occurrence of severe hypoxemia; (d) occurrence of a second episode of COPD exacerbation (either or not requiring mechanical ventilation); (e) 28-day all cause death. By analyzing the relevant epidemiological literature on COPD exacerbations [23–33] and on their complications [34–37] we could determine that these five elements are the most common complications in hospitalized AECOPD patients.
**Prolonged mechanical ventilation** is defined as mechanical ventilation (invasive and non-invasive) applied for ≥ 14 days uninterrupted for more than 48 hours.**Septic shock** is defined by the presence of (a) sepsis (organ dysfunction caused by proven infection with an increase in the Sequential Organ Failure Assessment (SOFA) score of 2 points or more); (b) need for vasopressors to maintain a mean arterial pressure of 65 mmHg or greater; (c) serum lactate levels greater than 2 mmol/l (>18mg/dl) in the absence of hypovolemia.**Severe hypoxemia** is defined as occurrence of a ratio of arterial-to-inspired oxygen O_2_ fraction (PaO_2_/FiO_2_) ≤ 150 with FiO_2_ of less than 0.6 and PEEP of at least 5 cm H_2_O for at least 12 hours.**Second episode of COPD exacerbation** is defined as occurrence of sustained (≥24 h) increase in cough, sputum production, dyspnea and arterial pH≤7.30 (either or not requiring mechanical ventilation).**28-day all-cause mortality** is defined at 672 hours from randomization. All patients will be classified as either “alive at Study Day 28” or, if dead, “dead at Study Day 28.” For example, day zero is the day of randomization and day 1 is the next day and encompasses all events that occur midnight-to-midnight, etc.

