### Sites and sites monitoring

The study will be conducted at up to twenty sites within Italy. Three site visits for each center will be performed (start of enrollment, mid-study, end of enrollment). Additional site visits will be performed as required. The coordinating center (University of Bologna – Policlinico S.Orsola-Malpighi) will supervise all aspects of the study and will be available to participant sites 24 hours, 7 days. All sites must have significant experience in treating AECOPD and with ECCO_2_R (i.e., all centers must routinely use continuous renal replacement therapy and perform at least 10 ECCO_2_R runs per year). Frequent investigators’ meeting will be planned in order to motivate enrollment. The coordinating center will provide logistic support to all participating sites in order to ensure efficient enrolment.

More specific data about sites can be obtained from the corresponding author.

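### The PaCO2 criterion for weaning from ECCO2R is wrong as written: it demands a fall of more than 80% from baseline, so the written rule leaves Group B no workable planned weaning route

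*Protocol article*

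**What the plan says.** The section Group B: Standard of care plus ECCO2R sets a planned weaning rule. The device is interrupted, with ventilation continued, "when all of the following are achieved for at least 12 hours". The four items are a respiratory rate below 25 breaths/min, pH above 7.35, "arterial PCO_2_<20% of the baseline value", and no accessory muscle use or paradoxical abdominal movement. The same section fixes the order: "Weaning from ECCO_2_R must always precede weaning from mechanical ventilation".

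A separate list gives the situations in which the device is stopped and removed: air embolus, clotting, malfunction, severe thrombocytopenia, low fibrinogen, or the treating physician's belief that the protocol may be harming the patient.

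On what the technique achieves, the Background says: "These systems are able to reduce PaCO_2_ by 20-25" per cent. No other section restates or corrects the PaCO2 criterion.

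**The concern.** A value below 20% of baseline is a fall of more than 80%. The criterion probably confuses a fall of 20% with a fall to 20%. All four items are required, so one unattainable item disables the whole planned route off the device. Through the ordering rule it also blocks the planned route off the ventilator.

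This happens in Group B only. Prolonged ventilation is a component of the primary outcome (it "is defined as mechanical ventilation (invasive and non-invasive) applied for ≥ 14 days"), and the analysis is by intention to treat. If the rule were followed literally, the bias would run against ECCO2R. If each site replaces it with its own reading, the experimental treatment is not the same across up to twenty sites.

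**Working it through.** **Inputs from the Protocol article**
- Written limit: below 0.20 × baseline (Group B).
- Expected reduction: 20-25%, so 0.75 to 0.80 × baseline remains (Background).
- Companion criterion: pH above 7.35 (Group B).
- Entry: "at least two of the following criteria for high risk of NIV-failure", one of which is pH ≤ 7.25 (Inclusion criteria). A patient may therefore enter with a pH above 7.25 by meeting the other two.
- A reference level of 60 mmHg, from the intubation criterion "PaCO_2_ greater than 60 mmHg" (Group A).

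**Assumptions**
- Baseline PaCO2 is not given. I use 60, 80 and 100 mmHg.
- Starting pH values of 7.15 to 7.32 are illustrative.
- Bicarbonate is constant unless stated.

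**Step 1. Limits under each reading (mmHg)**

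| Baseline | As written, < 0.20 × | At least 20% below, ≤ 0.80 × | Within 20% of, ≤ 1.20 × | Left after a 20-25% fall |
|---|---|---|---|---|
| 60 | 12 | 48 | 72 | 45-48 |
| 80 | 16 | 64 | 96 | 60-64 |
| 100 | 20 | 80 | 120 | 75-80 |

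The expected reduction leaves 0.75/0.20 = 3.75 to 0.80/0.20 = 4 times the written limit. This ratio does not depend on the baseline.

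**Step 2. Consistency with the pH criterion**

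With constant bicarbonate, pH_new = pH_0 − log10(PaCO2_new / PaCO2_0). At a ratio of 0.20 the rise is 0.699.
- Start 7.15: 7.849
- Start 7.25: 7.949
- Start 7.30: 7.999

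A 20-25% fall from 7.25 gives about 7.35 to 7.37. That sits at the companion criterion and suggests that a fall of at least 20% was meant.

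**Step 3. Does the choice between the two sensible readings matter?**

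The ratio needed to reach pH 7.35 is 10^(pH_0 − 7.35).

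| Starting pH | Ratio | Fall needed |
|---|---|---|
| 7.15 | 0.631 | 36.9% |
| 7.20 | 0.708 | 29.2% |
| 7.25 | 0.794 | 20.6% |
| 7.28 | 0.851 | 14.9% |
| 7.30 | 0.891 | 10.9% |
| 7.32 | 0.933 | 6.7% |

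The crossover with the 0.80 limit is 7.35 + log10(0.80) = 7.253. At 7.25 or below, pH is the binding criterion, both readings are already met, and weaning time is the same. Above 7.253, the reading of at least 20% below asks for more. From pH 7.30 and 80 mmHg, the reading of within 20% allows weaning at 80 × 0.891 = 71.3 mmHg; the other requires 80 × 0.80 = 64 mmHg.

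**Step 4. Two other ways the readings separate**
- *Rising bicarbonate.* pH stops binding when bicarbonate is multiplied by more than 0.80 / 10^(pH_0 − 7.35): 1.007 from 7.25, 1.130 from 7.20 and 1.268 from 7.15. These are rises of 0.7%, 13.0% and 26.8%.
- *Baseline read as the patient's usual PaCO2* (assumed 50 mmHg). The limits become 0.80 × 50 = 40 and 1.20 × 50 = 60 mmHg.

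**The case against.** The strongest reply is that this is a drafting slip that clinicians will read through. Sites must "perform at least 10 ECCO_2_R runs per year", and such teams will not aim for a PaCO2 of 12 to 20 mmHg. The Background and the pH criterion both point to the intended meaning, and the physician can always stop the device. For patients entering at pH 7.25 or below, the two sensible readings lead to the same weaning time if bicarbonate is constant. Reading the limit as within 20% of a pre-treatment gas is also weak, since it would allow a PaCO2 above the starting value. Finally, this is an article, and the full protocol may have the criterion right.

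Much of this stands. Literal adherence is unlikely, the difference between sensible readings is confined to some patients, and no effect on the primary outcome is demonstrated. The exact definition of baseline may also sit in the full protocol or the schedule of assessments, so I rest nothing on its absence here.

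Three points remain. The article does give a threshold, and it is wrong. The physician stop is a safety exit listed with air embolus and clotting, not a planned way to wean a recovering patient. And a rule that works only when sites silently replace it does not standardise the experimental treatment.

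**Conclusion.** The criterion is wrong as written and should be corrected. It asks for a fall of more than 80% where the protocol expects 20-25%, and this holds at any baseline PaCO2. The pH figures rest on constant bicarbonate, and the limits in mmHg on assumed baselines apart from the 60 mmHg reference level.

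The practical consequence is uncertain. Any bias from literal adherence would be against ECCO2R, and its size cannot be estimated from the document. The likelier result is that sites use different readings. These diverge only when entry pH is above about 7.25, when bicarbonate rises enough, or when baseline is taken as the usual PaCO2. The proportion of such patients is not given.

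**What to change.** Check whether the full protocol carries the same wording. Before the first patient, have the criterion read: arterial PCO2 at least 20% below baseline (at or below 80% of baseline), with baseline defined as the last blood gas before ECCO2R starts. The investigators should confirm that this is the threshold they intend, and all sites should be notified.

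The cost is a one-line correction and a site notice. Trial status says recruitment had not begun at the time of writing. Sample size, outcomes and analysis are unchanged.
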